### Interim analysis

Two interim analyses of drug tolerance and efficacy will be performed 6 months after the trial enrollment starting, and when 75% of participants have been enrolled in the trial, respectively. The level of significance will maintain an overall *P* value of 0.05 and be calculated according to the O’Brien-Fleming stopping boundaries. [16]

The DSMB will be instituted as an independent group of experts that will advise the clinicians and the study investigators, without direct involvement in the conduct of the study, nor financial, proprietary, professional, or other interests that may affect impartial, independent decision-making. The ISMETT Director of the Department for the Treatment and Study of Abdominal Diseases and Abdominal, the ISMETT Medical and Scientific Director and the primary investigator (PI) will have primary responsibility for the DSMB formation and for identifying the DSMB Chair and the terms of membership for the entire duration of the study. The DSMB will deliberate processes, including event triggers that would call for an unscheduled review, stopping guidelines, unmasking (unblinding) and voting procedures prior to initiating any data review. ISMETT investigators will collect, assess, report, and manage solicited and spontaneously reported adverse events and other unintended effects of trial interventions or trial conduct.

### Randomization

A statistician group, with no clinical involvement in the trial, will computer-generate a stratified block randomized sequence, based on D-MELD score [17–19]. This list will remain concealed from the trial coordinator at all times. When a DBD becomes available, the trial coordinator will assess the previously enrolled participant, which was considered suitable for the above-mentioned DBD [19]. S/he will obtain the treatment allocation by a specific website, dedicated for electronic clinical report form depository (https://simvalt.fullcro.org/). S/he will then inform the appropriate donor nursing and medical staff who will deliver the intervention(s). The trial coordinator will not collect outcome data, deliver the intervention(s), or provide patient care.

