### Outcomes

The primary outcome measure in this trial is postoperative graft survival after LT. The secondary outcomes of interest are patient survival, hospitalization stays, and all transplant-related complications in terms of the multi-tier Clavien grading system after LT. The grading system is used in order to identify a significant relation into two homogenous groups of liver transplanted patients, which only differ for Simvastatin or non-administration regimen utilizing the same procedure, with identical surgical instruments, and medical and nursing skilled staff. Baseline data on graft function and patient performance status will be collected immediately prior to discharge from the recovery unit (T0). Follow-up measures will be collected at three time points**:** 3-month (T1), 6-month (T2) and 12-month (T3)**,** after LT (see Fig. 1). All participants will be routinely evaluated with a post-reperfusion liver biopsy (sample), intensive care monitoring, daily laboratory and ultrasound examinations for the first week after the operation and when required during their hospital stay.

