### Sample size

We hypothesize that Simvastatin’s protective effects may occur in the liver during the harvesting procedure from the deceased donor and could significantly ameliorate post-LT outcomes. To reach the above-mentioned goals, we decided to recruit 106 patients. This sample size achieves 90% power to detect a difference of 14.6% between the two groups survival using a one-sided binomial test. The target significance level is 0.05. These results assume a null hypothesis that the proportion of the group with the standard procedure is 0.85.

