#### Statistical analysis

Intention-to-treat analysis will be applied. Quantitative variables will be compared with the Student t-test or the Wilcoxon rank-sum test and categorical variables will be compared with the chi-squared test or Fisher’s exact test as appropriate. No a-priori criteria will be set for an early end of the study. Data will be analyzed according to the 2 × 2 randomized factorial study design. All of the phases will follow the Consolidated Standards of Reporting Trials 2010 Statement to improve the reporting of parallel-group randomized controlled trial, enabling readers to understand the trial’s design, conduct, analysis. and interpretation as well as to assess the validity of its results. It will be achieved through complete transparency from study investigators. All analyses and graphics were performed in the R statistical computing environment, version 3.4.3.

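### Allocation is stratified by D-MELD but every named test is unstratified: mildly conservative if D-MELD is prognostic, with almost no power cost at the design effect

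*Protocol article*

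**What the plan says.** All references are to the Protocol article.

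- **Randomization:** statisticians outside clinical care will "computer-generate a stratified block randomized sequence, based on D-MELD score". The article does not give cut-points, number of strata or block size.
- **Outcomes:** "The primary outcome measure in this trial is postoperative graft survival after LT". Follow-up is at 3, 6 and 12 months.
- **Statistical analysis:** the rule that would cover a survival proportion is that "categorical variables will be compared with the chi-squared test or Fisher’s exact test as appropriate". Continuous measures get a t-test or a rank-sum test. No stratified test and no model containing D-MELD is named. No test is assigned to graft survival by name.
- **Sample size:** "This sample size achieves 90% power to detect a difference of 14.6% between the two groups survival using a one-sided binomial test". The calculation uses one survival proportion per group and makes no reference to strata.
- **Interim analysis:** efficacy is examined 6 months after enrolment starts and again at 75% enrolment.

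**The concern.** Stratified blocks force the arms to be alike on D-MELD. If D-MELD is prognostic, this removes part of the chance variation in the difference between arms. A test that pools over D-MELD still counts that variation in its standard error. It is therefore conservative: its true type I error lies below the nominal level, and some power may be lost. D-MELD is the only stratification factor named, which suggests that the investigators believe it matters for outcome, though the article does not say how strongly.

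A secondary point concerns incomplete follow-up. The named tests compare values or proportions and cannot use partial follow-up on a survival outcome. At the first interim look no recipient can have completed 12 months. At the second, the most recently transplanted cannot have done so.

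**Working it through.** **1. The plan's own figure.** Inputs from Sample size: control survival 0.85, difference 0.146 (so 0.996 on simvastatin), one-sided alpha 0.05, power 90%. Equal allocation is assumed. With unpooled variances:

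n per arm = (1.645 + 1.282)² × (0.85×0.15 + 0.996×0.004) / 0.146² = 8.564 × 0.131484 / 0.021316 = 52.8

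This rounds to 53 per arm, or 106 in total, with power 90.1%. The stated 106 therefore reproduces as an unstratified comparison of two proportions. (The pooled-variance version gives 112.)

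**2. Approximate size when strata are ignored.** Let r be the within-stratum variance divided by the total variance. With the arms balanced within strata, a nominal one-sided 5% unstratified test has true size of about 1 − Φ(1.645/√r). Assume two strata with 40 and 13 recipients per arm. For stratum survival of 90% and 70%:

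- mean survival = (40×0.90 + 13×0.70)/53 = 0.851
- within-stratum variance = (40×0.09 + 13×0.21)/53 = 0.1194
- total variance = 0.851 × 0.149 = 0.1268
- r = 0.1194/0.1268 = 0.942, and 1.645/√0.942 = 1.695, so the size is about 4.5%

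The same steps give r = 0.885 and 4.0% for 92/64, and r = 0.765 and 3.0% for 95/55.

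**3. Simulation.** At least 200,000 trials per scenario, 40+13 per arm, one-sided 0.05, pooled z test against CMH without continuity correction. All stratum rates are assumptions, chosen to average about 85%. The power columns use a treatment odds ratio of 3 in each stratum.

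| Stratum survival, % | Odds ratio between strata | Size, unstratified | Size, CMH | Power, unstratified | Power, CMH |
|---|---|---|---|---|---|
| 87/79 | 1.8 | 4.8% | 4.8–4.9% | 49.2% | 49.4% |
| 88/76 | 2.3 | 4.7% | 4.9% | 48.7% | 49.2% |
| 90/70 | 3.9 | 4.4–4.5% | about 5% | 47.0% | 48.5% |
| 92/64 | 6.5 | 4.0% | about 5% | 44.7% | 47.9% |
| 95/55 | 15.5 | 2.9% | about 5% | 38.6% | 45.3% |

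With equal strata (85/85) the two tests do not differ materially. Ranges show the spread between repeat runs.

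**4. Power at the design effect (85% vs 99.6%).** Unstratified against CMH: 97.1 vs 97.1% (90/70), 97.2 vs 97.2% (92/64) and 97.3 vs 97.4% (95/55). The gain is at most about 0.1 points.

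**5. A second set of assumptions.** Here total N is 106, blocks of 4 are used within two strata, and stratum sizes are random. Three scenarios use equal-sized strata (90/80, 95/75, 98/72) and one has 20% of recipients at high risk (90/65). Unstratified size is 4.9%, 4.4%, 4.0% and 4.4%, against 5.0–5.1% for CMH. The power gain is at most 0.2 points at the design effect. At 85% vs 95% it runs from nil (55.3 vs 55.2%) to about 2 points (55.7 vs 58.0%).

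**The case against.** The strongest case against acting has four parts.

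- **The size of the effect is assumed.** The article gives no outcome by D-MELD. At 87/79 or weaker the difference all but disappears, and strata as far apart as 95/55 are extreme. This stands, and it is why the whole range is shown.
- **There is no real power loss at the planned effect.** A reader might infer from a figure such as 38.6 against 45.3% that the trial gives away substantial power. That needs both extreme strata and an odds ratio of 3. The design effect corresponds to an odds ratio of about 44: (0.996/0.004)/(0.85/0.15). There the gain is about 0.1 points. The choice within the named tests matters far more: at 53 per arm and the design effect, Fisher's exact test has exact one-sided size 2.9% and power 87.1%, against 4.9% and 97.1% for chi-squared.
- **The article is condensed.** Adjustment for strata may appear in a full protocol or analysis plan, and the tests are listed generically by type of variable. This limits the point but does not remove it. The article does name its tests, and none of them matches the allocation scheme. That graft survival will be tested as a single proportion per arm is an inference from Sample size and Statistical analysis read together.
- **Fixed-time survival is a legitimate proportion.** A reader might infer that the final analysis must drop or guess censored recipients. The documents do not support that: all recipients can have reached 12 months by then, and no loss to follow-up is stated. Incomplete 12-month follow-up is certain only at the interim looks.

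The mismatch also poses no threat to a positive result, because a conservative test does not inflate false claims of benefit.

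**Conclusion.** The mismatch between stratified allocation and unstratified tests is in the text, and its direction is clear: if D-MELD predicts graft survival, the named tests are mildly conservative. Under the assumed strata the true one-sided size ranges from about 4.8–4.9% (null or weak) through 4.4–4.5% and 4.0% (strong) to 2.9% (extreme). A stratified test holds about 5%. The power gain is about 0.1 points at the design effect. It is 0 to 3 points at an odds ratio of 3, rising to about 7 only with 95/55 strata.

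These figures rest on 1:1 allocation, two strata, no dropout and stratum survival rates that the documents do not give. Confidence is high in the direction and moderate at best in the size. This is a nearly free improvement of low to moderate priority, not a flaw that undermines the trial.

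**What to change.** In Statistical analysis, state that the primary comparison of 12-month graft survival is stratified by the D-MELD strata used for allocation. Either of these would serve:

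- a CMH test, if 12-month status is known for all; or
- a stratified log-rank test with Kaplan-Meier 12-month estimates, which also uses recipients with partial follow-up at the two interim looks.

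Report the D-MELD-stratified 12-month difference with its confidence interval, and use the same strata for patient survival. Fix the choice before any unblinded data are seen.

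The cost is a sentence or two of text and a few lines of R. The strata are needed for allocation and so are already recorded, and the sample size of 106 need not change. The number of strata should be kept small, because events will be few.

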**Patient and methods:**

We propose a prospective, double-blinded, randomized phase 2 study of 2 parallel groups of eligible adult patients. We will compare 3-month, 6-month, and 12-month graft survival after LT, in order to identify a significant relation between the two homogenous groups of LT patients. The two groups only differ by the Simvastatin or placebo administration regimen while following the same procedure, with identical surgical instruments, and medical and nursing skilled staff. To reach these goals, we determined that we needed to recruit 106 patients. This sample size achieves 90% power to detect a difference of 14.6% between the two groups survival using a one-sided binomial test.

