## Methods

### Trial design

The trial will employ a randomized administration of a single oral dose of 80 mg of Simvastatin (Sandoz®, Holzkirchen, Germany) (Group 1) or placebo (Group 2) per adult cadaveric donor through a nasogastric tube 1 h before the organ procurement, to investigate the effect of these interventions on graft survival after LT.

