### Setting

The trial will be conducted in the operating rooms of a private hospital in Palermo (ISMETT), Italy and in every external hospital where all of the eligible DBDs are located. ISMETT was developed specifically for transplantation through a partnership of the Sicilian regional government and the University of Pittsburgh Medical Center. It is the first hospital in Southern Italy certified by Joint Commission International for excellence in clinical practice and is one of the first hospitals in Italy to use an entirely computerized process. It includes laboratories for clinical chemistry, microbiology, immunology and pathology, as well as laboratories that are equipped to support research activities. Liver transplantation is at the core of ISMETT transplantation programs. The ISMETT Abdominal Surgery and Transplantation operational unit has a team of 6 expert attending physicians and 2 surgery fellows, who manages the selection and care of patients requiring LT both from cadaveric and living donor. In ISMETT there is close collaboration and daily interdisciplinary teamwork with colleagues from other disciplines at ISMETT, including hepatologists, critical care clinicians, radiologists, endoscopists, and researchers from Ri.MED Foundation. An intense daily collaboration is performed with nurses, physical and respiratory therapists. One skilled research nurse will be recruited for guaranteeing the correct schedule of outpatient visit examinations, patient appointments and maximize the adherence. Ri.MED investigator will coordinate the effective functioning of the data and safety monitoring board (DSMB), maintaining information reviewed, discussed and recorded with the strict confidentiality. In addition, she will ensure the correct data recording of retrieval procedures, patient enrolment and data analysis in agreement DSMB recommendations and respect of the entire study phases.

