### Interventions

Participants will be allocated to one of two groups (see Fig. 1): Group one will receive an organ procured in a DBD after preoperative administration of Simvastatin; group two will comprise the control group receiving no DBD intervention before the standard organ procurement in a DBD or after.

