#### Usual care

Patients in group two will receive ‘usual care’ only. Placebo will include the aforementioned preoperative administration of 2 hard jelly capsules (dimension = 0), containing an orange-swedish microcrystalline cellulose.

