### Blinding

Outcome measures will be collected by recovery unit medical and nursing staff that are blinded to the participants’ treatment allocation. The interventions will be delivered by separate groups of operative staff (operative donor team), and each group will be blinded to the treatment delivered by the other. The trial will adhere to procedures to maintain separation between the data management staff who will record the outcome data and the donor operative nursing and medical staff who will deliver the intervention(s).

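### The declared double blinding is not supported by the described procedures, and the control arm is both a placebo and no donor intervention

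*Protocol article*

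**What the plan says.** **Masking claim.** The title has the word double-blinded, and the abstract repeats it: "We propose a prospective, double-blinded, randomized phase 2 study of 2 parallel groups of eligible adult patients".

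**Route of the allocation.** Under Randomization, the sequence is concealed from the trial coordinator. When a donor becomes available and a suitable enrolled recipient has been identified, "S/he will obtain the treatment allocation by a specific website". The next step is "S/he will then inform the appropriate donor nursing and medical staff who will deliver the intervention(s").

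**Who is masked.** Blinding, repeated almost word for word in Monitoring, says that recovery-unit staff collect outcomes without knowing the allocation, and that data management staff are kept apart from donor staff. For the groups that deliver treatment the only statement is "each group will be blinded to the treatment delivered by the other".

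**The control.** Trial design gives the donor simvastatin "or placebo (Group 2) per adult cadaveric donor through a nasogastric tube 1 h before the organ procurement". Interventions says "group two will comprise the control group receiving no DBD intervention before the standard organ procurement". Usual care first says that group two has usual care only, and then "Placebo will include the aforementioned preoperative administration of 2 hard jelly capsules". Purpose and Outcomes contrast simvastatin with non-administration.

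**The concern.** A double-blind claim tells readers that those who could influence the result do not know the arm. Here the coordinator receives the allocation itself and then speaks to the staff who dose the donor. Nothing in the article says that what is passed on is coded. Dosing takes place about an hour before procurement, after a recipient has been matched, so any donor-side staff who know the arm hold that knowledge while the graft is handled and before it is transplanted. Whether a dosed graft is used is then a decision made after randomisation.

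The control arm raises a separate question. A placebo comparison and a comparison with no intervention are different trials as regards masking. A reader cannot tell from the article which one is being run.

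**Working it through.** **Step 1. Set the control descriptions side by side.**

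| Section | Control arm |
|---|---|
| Abstract, Patient and methods | placebo |
| Trial design | placebo by nasogastric tube, 1 h before procurement |
| Usual care | usual care only, followed by two placebo capsules |
| Interventions | no donor intervention, before or after procurement |
| Purpose; Outcomes | non-administration |

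The first two rows cannot hold together with the last two, and the middle row contains both. If Interventions is followed as written, the donor team knows the arm from whether anything is given, whatever the website displays.

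**Step 2. Go through the roles.**

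- Outcome collectors: stated to be masked.
- Data management staff: separated from donor staff.
- Coordinator: obtains the treatment allocation. Concealment of the list protects future assignments, not the current one.
- Donor staff: informed by the coordinator, content unstated. No kit number or pack code is mentioned.
- Recipients: no explicit statement.

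The sentence about each group and the other presupposes at least two separately delivered interventions. There is one. The sentence would suit a factorial trial, and Statistical analysis and Discussion do use factorial wording, but the design described has two parallel groups. Read literally, it leaves each team aware of its own treatment.

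**Step 3. Compare the products.** Under Experimental treatment, the active capsules are emptied into a hydro-alcoholic suspension for the tube. Under Usual care, the placebo is two capsules of coloured cellulose. A matching vehicle and appearance are not stated.

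**Step 4. Illustrate fragility.** Inputs from Sample size: N = 106, control survival 0.85, difference 0.146 (so 0.996 on simvastatin), one-sided alpha 0.05, power 90%. 1:1 allocation is assumed.

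The planned size is reproduced with the unpooled formula:

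n per arm = [0.85 × 0.15 + 0.996 × 0.004] × (1.645 + 1.282)² / 0.146² = 0.1315 × 8.564 / 0.02132 ≈ 52.8, so 53 per arm and 106 in total.

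Expected losses are 53 × 0.15 = 7.95 on control and 53 × 0.004 = 0.21 on simvastatin. Fisher's exact test with 53 per arm and 8 control losses gives:

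| Simvastatin losses | One-sided p | Two-sided p |
|---|---|---|
| 0 | 0.003 | 0.006 |
| 1 | 0.016 | 0.031 |
| 2 | 0.046 | 0.093 |
| 3 | 0.101 | 0.201 |

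At the boundary one graft moves the result across 0.05: between 2 and 3 losses one-sided, and between 1 and 2 two-sided. From the planned alternative (8 v 0), three added simvastatin losses are needed to lose one-sided significance. The table counts losses. It does not model a declined graft, which changes who is transplanted and is not itself a graft loss.

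**The case against.** The strongest reply is that the article never says donor staff are told the arm. The verb inform has no object. Being told that randomisation has occurred, or which pack to use, fits the sentence. Pack labelling is detail that an article may leave to the full protocol or the product dossier. Monitoring restricts unblinding to severe unexpected reactions, which suggests that a working code exists. This stands in part: it would be too strong to infer that donor staff are shown to be unmasked, or that the trial is open-label. It does not remove the point, because what the coordinator obtains is named as the treatment allocation and no code is mentioned.

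Four further readings are tempting and are not supported.

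- *The placebo is prepared differently.* Usual care refers back to the administration already described, and Trial design gives the placebo the same tube and timing. A parallel preparation is likely. Matching is unstated, which is not the same as a stated difference.
- *The dosing staff also accept grafts, re-list, grade complications and discharge.* Setting describes a unit that "has a team of 6 expert attending physicians and 2 surgery fellows, who manages the selection and care of patients requiring LT". Blinding refers to a separate donor operative team, donor procedures also take place in external hospitals, and Randomization bars the coordinator from outcome collection and care. Overlap is possible but not documented.
- *Outcome masking lapses before 12 months.* The statement covers outcome measures without a time limit.
- *One or two influenced decisions would reverse the result.* That holds only if the result already lies at the boundary.

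Two safeguards also count. The recipient is judged suitable before the allocation is obtained, and intention-to-treat is specified. Both limit selection after allocation, but neither removes it at the final decision to use the graft.

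None of these replies resolves the contradiction about the control arm. That is not missing detail: the article gives incompatible descriptions of the comparator.

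**Conclusion.** The point holds in two parts, with different strength. That the control arm is described in incompatible ways is certain from the text, and if controls receive no donor intervention, donor-team masking is impossible. That the double-blind label lacks support is also clear, because no described procedure masks the coordinator or the dosing staff. Whether those staff in practice learn the arm is not established.

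The exposure is mainly on the donor side: handling and use of the graft after allocation. Bias in outcome collection is a lesser worry, given the declared masking of collectors and a fairly objective primary outcome. No figure in the article measures the bias. The Fisher results, which assume 53 per arm and 8 control losses, show only that a borderline result would depend on a single graft. The point should be settled because it concerns the comparator and the headline masking claim.

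**What to change.** 1. Have the website return a kit code only, so that neither the coordinator nor the donor team learns the arm.
2. Reconcile Purpose, Interventions, Usual care and Outcomes with the abstract and Trial design so that one control is described throughout. If it is the placebo, state that its preparation and appearance match the active product.
3. In Blinding and Monitoring, replace the sentence about each group and the other with a list of the roles that are masked: coordinator, donor team, recipient, recipient team and outcome assessors, and for how long.
4. Report by arm the number of dosed grafts not transplanted.
5. Recruitment has been open since 30 June 2018, so record what the donor staff were actually told. If they were told the arm, describe the trial as outcome-assessor-blinded instead of double-blind.

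The cost is a website setting, kit labelling, some pharmacy work on matching if a placebo is used, and wording. Placebo capsules are already described, and the sample size does not change.
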